
**Fig. 1 Fig1:**
[figure not shown]
Study outline

### Assessments

The pain intensity, cognition function, insanity, anxiety, and depression in the patients will be assessed using a standardised and validated questionnaire. Before enrolment, the patients will be treated in anaesthesia evaluation clinics and screened according to the inclusion criteria and informed consent (Additional file 1). The demographic characteristics of the patients (age, gender, height, weight, medical history, medication history, allergy history, ASA grade, and sleep condition) will be collected, and physical characteristics, blood pressure, heart rate, and oxygen saturation of blood will be measured and recorded as Tbase. Preoperative examinations (urinalysis, haematological examination, and electrocardiogram) will be conducted to validate cardiac, liver, kidney, and coagulation functions. Pain intensity will be evaluated using the numerical rating scale. Anxiety and depression will be assessed using hospital anxiety and depression scale (HADS). Cognition function was assayed through mini-mental state evaluation (MMSE).

On the day of the operation, the vital signs, including blood pressure, heart rate, pulse oxygen saturation, and respiratory rate, will be measured and recorded when the patient entering the operating room and after induction and endoscope entrance, Afterwards, these signed will be recorded every 3 min until the patient left the room. The drug doses of anaesthesia, administration route, anaesthesia time, operation type, operation time, times of biopsy, infusion quantity, blood loss, and satisfaction of endoscopist (satisfied, average, or dissatisfied) will be documented. The vital signs of the patients in the recovery room will be recorded after every 5 min. MMSE scores will be re-evaluated before the patient leaves the recovery room, and the patients will be asked about their satisfaction degree (satisfied, average, or dissatisfied) and the operation and pain severity (0 point represents absolute no pain; 10 points denote unbearable pain). The incidence of adverse events (dizziness, headache, cardiopalmus, dyspnoea, mobility, nausea, and vomiting) will be followed up through phone calls after 0.5 h, 2 h, 1 day, 2 days, 3 days, 1 week, 1 month, and 6 months of the operation. The information about sleep conditions will be collected, and the alterations of MET scores, MMSE scores, HADS scores (the details of any specific manifestations will be inquired) will be assessed.

Adverse events will be assessed and treated throughout the study. When the perioperative oxygen saturation of blood < 95%, the anaesthesiologists will raise the lower jaw and open airway; this phenomenon is defined as insufficient oxygen supply. The condition of the oxygen saturation of blood of < 90% is defined as hypoxemia. When the oxygen saturation of blood < 88%, the endoscope will be removed, and the patient will be fitted with the mask for 100% pure oxygen inhalation and respiration will be assisted using a balloon. Simultaneously, adverse events, such as cough, laryngospasm, low and high blood pressure, bradycardia, and tachycardia triggered by drugs or operation, will be documented. Postoperative adverse events, including nausea, vomiting, dizziness, oversedation, infection, nightmare, diarrhoea, insanity, blurring of vision, nystagmus, and hallucination, will be recorded in detail.

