### Endpoints

The primary endpoints include the frequency of tussis, nausea and vomiting, and/or body movements observed at the insertion of the endoscope into the pharyngeal cavity or within 5 min of endoscope insertion. Secondary endpoints are as follows: (1) the time of the addition of the first drug, from the end of induction to the addition of the first drug (from the injection of the study medication to the disappearance of eyelash reflex); (2) the time of recovery from anaesthesia, from the end of the operation till the patient left the recovery room (the end of operation to consciousness return); (3) perioperative propofol doses; (4) incidence of perioperative adverse events, including tachycardia, oxygen desaturation (the time of 90% ≤ SpO_2_ < 95% for more than 10 s), breathing inhibition (the time of SpO_2_ < 95% for more than 15 s), bradycardia (< 50 beats per minute or a decrease in HR of 20% or more from baseline), and high and low blood pressure (blood pressure < 30% of the basal blood pressure or systolic blood pressure or blood pressure > 30% of the basal blood pressure); (5) incidence of postoperative adverse events (within 6 months after the operation) including nausea, vomiting, increased secretion, dizziness, over sedation, infection, nightmare, uneasiness, itching, disorientation, insanity, breathing inhibition, diplopia, diarrhoea, intestinal obstruction, urinary retention, gastroesophageal reflux, constipation, shiver, and hallucination; (6) MMSE scores, MET scores, and sleep condition after 0.5 h, 2 h, 4 h, 1 day, 2 days, 3 days, 1 week, 1 month, and 6 months of the operation; (7) pharmacoeconomic outcomes (calculated incremental cost-effectiveness ratio based on cost-effectiveness analyses).

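### The article's three postoperative adverse-event lists disagree: the telephone list names 3 of the 20 events in the 6-month endpoint, and 11 of the 20 are on neither collection list

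*Protocol article*

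**What the plan says.** The protocol article lists postoperative adverse events in three places.

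- **Endpoints, secondary endpoint (5).** The window is 6 months and 20 events are named: "incidence of postoperative adverse events (within 6 months after the operation) including nausea, vomiting, increased secretion, dizziness, over sedation, infection, nightmare, uneasiness, itching, disorientation", continuing with "insanity, breathing inhibition, diplopia, diarrhoea, intestinal obstruction, urinary retention, gastroesophageal reflux, constipation, shiver, and hallucination".
- **Assessments, follow-up.** "The incidence of adverse events (dizziness, headache, cardiopalmus, dyspnoea, mobility, nausea, and vomiting) will be followed up through phone calls". The calls are made "after 0.5 h, 2 h, 1 day, 2 days, 3 days, 1 week, 1 month, and 6 months of the operation", which is eight contacts. Sleep condition, MET, MMSE and HADS are also followed, and for these "the details of any specific manifestations will be inquired".
- **Assessments, adverse-event paragraph.** It opens with "Adverse events will be assessed and treated throughout the study" and ends with an 11-item list: "Postoperative adverse events, including nausea, vomiting, dizziness, oversedation, infection, nightmare, diarrhoea, insanity, blurring of vision, nystagmus, and hallucination, will be recorded in detail". It does not say when these items are collected or by what kind of contact.

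The article describes no other scheduled adverse-event contact after discharge.

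**The concern.** An incidence over 6 months is only as complete as the questions put to patients during those months. A caller working from the printed telephone list would prompt for few of the events that the endpoint then reports. Patients tend to mention unprompted symptoms less often than symptoms they are asked about, so low counts for unprompted events could be mistaken for good tolerability. This matters because the Discussion presents tolerability and safety in practice as open questions that the trial is meant to answer.

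**Working it through.** **Step 1. Compare the lists.** Terms are matched by name, with the two spellings of oversedation treated as one. The inputs are endpoint (5) with 20 terms, the telephone list with 7, and the recording list in the adverse-event paragraph with 11.

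| Where the event is named | Events | Count |
|---|---|---|
| Endpoint and both collection lists | nausea, vomiting, dizziness | 3 |
| Endpoint and recording list only | oversedation, infection, nightmare, diarrhoea, insanity, hallucination | 6 |
| Endpoint only | increased secretion, uneasiness, itching, disorientation, breathing inhibition, diplopia, intestinal obstruction, urinary retention, gastroesophageal reflux, constipation, shiver | 11 |
| Telephone list only | headache, cardiopalmus, dyspnoea, mobility | 4 |
| Recording list only | blurring of vision, nystagmus | 2 |

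Checks: endpoint 3 + 6 + 11 = 20; telephone list 3 + 4 = 7; recording list 3 + 6 + 2 = 11.

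Coverage of the endpoint is 3/20 by the telephone list, 9/20 by the recording list, and 9/20 by the two together, because the telephone list adds nothing to the other. If dyspnoea is read as breathing inhibition, the telephone list covers 4/20 and the two lists together 10/20.

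**Step 2. Ask which of the 11 could be caught another way.**
- Increased secretion, breathing inhibition and shiver would mostly occur in the recovery room, under observation.
- Uneasiness and disorientation may come up through the HADS, MMSE or sleep inquiry.
- That leaves 11 − 5 = 6: itching, urinary retention, constipation, reflux, intestinal obstruction and diplopia. Neither collection list names them, and no listed scale is described as covering them. Reading blurred vision as diplopia would still give it no telephone prompt.

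**Step 3. What incomplete capture would do.** The article states no event rate, capture rate or power for this endpoint, so there is no figure to reproduce. Suppose the same fraction s of events is captured in both arms. The observed rates are then s·p1 and s·p2. Their ratio is unchanged, and their difference shrinks to s·(p1 − p2). Power of a two-sided Fisher exact test at 0.05, with 100 per arm and **assumed** true rates of 15% and 3%:

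| Capture s | Observed rates | Difference | Power |
|---|---|---|---|
| 1.0 | 15% v 3% | 12 points | 82% |
| 0.7 | 10.5% v 2.1% | 8.4 points | 62% |
| 0.5 | 7.5% v 1.5% | 6 points | 40% |
| 0.3 | 4.5% v 0.9% | 3.6 points | 15% |

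The starting value depends on the rates chosen. With assumed rates of 5% and 2%, power is about 10% even at full capture. The table shows the direction of the effect and does not estimate the loss in this trial.

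**The case against.** The strongest reply is that the article does not confine the calls to the seven symptoms. It says adverse events are assessed throughout the study, and its recording list is introduced as open-ended. A journal article also normally leaves the call script to the full protocol or case report form. Much of this stands, and it rules out three stronger readings that a reader might be tempted to make.

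- *That nightmare and hallucination go uncollected.* Both are named on the recording list. What is missing for them is a time and mode of collection.
- *That 17 of the 20 events (20 − 3) rest on spontaneous reports.* Six of those 17 are on the recording list. Assessments says that insanity is assessed by questionnaire, and sleep, MMSE and HADS are followed with active inquiry. Several other events belong mainly to the recovery room. The text on the calls speaks of following events up and the other list of recording them, so the choice of verb does not show that one is prompted and the other is not.
- *That the safety comparison is biased between arms, or that events are known to be under-counted.* Randomisation and blinding states that recovery-room data collection and follow-up are blinded, and one schedule is described for all arms. The article gives no capture rate, so under-counting is a reasonable expectation and not an established fact.

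The appeal to the full protocol does not dispose of the point. The article does not leave the list to another document: it prints three lists for overlapping follow-up, and they conflict.

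**Conclusion.** The point holds as an inconsistency with a practical consequence. The three lists need reconciling: the telephone list names 3 of 20 endpoint events (4 on the generous reading), the recording list names 9 without saying when or how they are collected, and 11 are on neither. Six of those 11 have no named collection route after discharge and are likely to be under-ascertained. That judgement assumes that callers follow the printed list and that unprompted symptoms are reported less often than prompted ones. The likely effect is low absolute rates and diluted differences between arms; its size cannot be derived from the article. The endpoint is a secondary safety outcome, and the primary analysis is not affected.

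**What to change.** Merge the three lists into one checklist: the 20 events of endpoint (5) plus the six outside it (headache, cardiopalmus, dyspnoea, mobility, blurring of vision, nystagmus), 26 items before any overlapping terms are combined. Ask it in the same words in all arms at every recovery-room and scheduled telephone contact, and report solicited and spontaneously reported events separately. The calls are already scheduled, so the cost is a slightly longer script and no new visits.

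If the planned dates were kept, recruitment ended on 1 April 2023 and the last 6-month call fell around 1 October 2023, before the article appeared in January 2024. If follow-up is indeed complete, what remains is a reporting change: state which events were actually solicited at which contacts, and present the others as spontaneously reported.

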### Endpoints

The primary endpoints include the frequency of tussis, nausea and vomiting, and/or body movements observed at the insertion of the endoscope into the pharyngeal cavity or within 5 min of endoscope insertion. Secondary endpoints are as follows: (1) the time of the addition of the first drug, from the end of induction to the addition of the first drug (from the injection of the study medication to the disappearance of eyelash reflex); (2) the time of recovery from anaesthesia, from the end of the operation till the patient left the recovery room (the end of operation to consciousness return); (3) perioperative propofol doses; (4) incidence of perioperative adverse events, including tachycardia, oxygen desaturation (the time of 90% ≤ SpO_2_ < 95% for more than 10 s), breathing inhibition (the time of SpO_2_ < 95% for more than 15 s), bradycardia (< 50 beats per minute or a decrease in HR of 20% or more from baseline), and high and low blood pressure (blood pressure < 30% of the basal blood pressure or systolic blood pressure or blood pressure > 30% of the basal blood pressure); (5) incidence of postoperative adverse events (within 6 months after the operation) including nausea, vomiting, increased secretion, dizziness, over sedation, infection, nightmare, uneasiness, itching, disorientation, insanity, breathing inhibition, diplopia, diarrhoea, intestinal obstruction, urinary retention, gastroesophageal reflux, constipation, shiver, and hallucination; (6) MMSE scores, MET scores, and sleep condition after 0.5 h, 2 h, 4 h, 1 day, 2 days, 3 days, 1 week, 1 month, and 6 months of the operation; (7) pharmacoeconomic outcomes (calculated incremental cost-effectiveness ratio based on cost-effectiveness analyses).

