The best approach to analgesia and sedation during upper GI endoscopy is controversial; thus, the development of an appropriate sedative/analgesic strategy that can influence the examination quality, patient cooperation, and degree of satisfaction towards anaesthesia is imperative. From the preliminary observations of clinical trials, we assumed that compared with single-use of propofol, a combination of propofol and small doses of sufentanil, esketamine, or lidocaine, especially the combination of propofol and esketamine, might reduce tussis incidence. To verify our hypothesis, this study expounded the effects of different drugs combined with propofol on tussis reflection in upper GI endoscopy.

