
### Intervention

Figure 1 presents the study outline. The patients are selected according to their inclusion and exclusion criteria for painless upper GI endoscopy and informed consent. The patients will be divided into the four groups: P group (single administration of propofol), P + S group (administration of propofol and sufentanil in combination), P + K group (administration of propofol and esketamine in combination), and P + L group (administration of propofol and lidocaine in combination) (*N* = 100 per group). Baseline information will be collected and recorded before the operation. Anaesthetic drugs will be prepared by the nurses and anaesthetists on the day of the operation as follows: 0.9% normal saline (20 mL) for the P group, 0.5 μg/mL sufentanil (20 mL) for the P + S group as a mixture, 1.5 mg/mL esketamine (20 mL) for the P + K group, and 10 mg/mL lidocaine (20 mL) for the P + L group. Before entering the operating room, the patients will be given lidocaine defoamer for gargling to open the upper limb vein and 5 mL/min lactate Ringer solution. After entering the room, the patients will wear masks to inhale high-flow oxygen, and their vital signs will be monitored and recorded as Tire. Analgesic drugs (diluted to 20 mL according to different concentrations) prepared by the nurses will be slowly injected into their veins 5 min before examination for 30 s with the dose of millilitre 10% kg of body weight, and then, 1.5 mg/kg propofol will be intravenously administrated. Multiple-dose administration is acceptable according to the state of the patient. The endoscope will be inserted when the eyelash reflex disappeared (sedation depth grade: deep sedation). Blood pressure will be recorded after every 3 min from the beginning of the examination, and HR, SpO_2_, and RR will be recorded simultaneously. The primary outcome was the frequency of tussis, nausea and vomiting, and/or body movements observed at the insertion of the endoscope into the pharyngeal cavity or within 5 min of endoscope insertion. When subclinical respiratory depression (90% ≤ SpO_2_ < 95%) occurred, the jaw-thrust manoeuvre was performed to open the airway. When hypoxia (75% ≤ SpO_2_ < 90% for less than 60 s) occurred, in addition to the jaw-thrust manoeuvre, the oxygen flow rate was increased from 2 to 6 L/min. In case of any abnormalities, notifications should be given, and appropriate doses of propofol should be added until the endoscope exits the teeth pad. During endoscopy, 2–4 mL of propofol should be added under the conditions of extended operation time, accelerated breathing, and elevated blood pressure and heart rate to maintain deep sedation. The patients will be transferred to a recovery room after the operation, and their vital signs will be recorded after every 5 min until the patients met the standard of leaving the hospital (Steward score ≥ 4) before discharge. For each patient, the anaesthesia protocol will be completely decided by an investigator based on their experience and expertise and clinical practice guidelines. The intervention was conducted by experienced health professionals under the supervision of researcher groups. In addition, randomly check was performed to make sure the adherence of the staff to the intervention protocols. There were no concomitant interventions that are prohibited during this trial. There is no compensation or post-trial care for participants.

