### Statistical methodology

Efficacy assessment is based on the intention-to-treat (ITT) population, which is defined as all randomised patients. Safety analyses will be performed in a safety evaluation set, which is a subset of all the patients exposed to a minimum of one dose of the studied medication. The SPSS 24.0 software will be used for statistical analyses. Significance will be analysed using two-sided tests, and *p* < 0.05 will be judged as the statistical significance standard. The normally distributed measurement data are presented as mean ± standard deviation (*x* ± *s*). The quartile method will be used to explain the measurement data with non-normal distribution. The repeated analysis of variance and Turkey test will be used for comparisons within a group and between multiple groups, respectively. Count data will be analysed using non-parametric tests, such as Rank-sum test, chi square test, and Fisher exact test. The multivariate regression analysis will be employed to explore the effects of different analgesic drugs combined with propofol on tussis during upper GI endoscopy. We will consider performing predefined subgroup analyses on the primary endpoints according to age, operation types, and special populations. Missing data will not be imputed. In addition, the primary endpoint analysis will also be conducted in a per-protocol set and compared with the ITT analysis to analyse sensitivity. No interim analyses are planned.

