### Sample size calculation

Based on the results of previous pretest, we speculated that compared with only propofol, the combination of small doses of esketamine with propofol could exhibit significant effect against tussis reduction incidence by a minimum of 15% during upper GI endoscopy. The type I error probability, power of test, and sample size ratio will be set to 0.05, 0.8, and 1:1, respectively. According to relevant literature reports, some believe that a sample size of 18 patients per group will provide 80% of the ability to detect differences between groups 15% difference at a level of *α* = 0.05. At *α* = 0.05, based on the 80% power difference of 15% difference in propofol demand between the levels and detection groups, the power was increased 90%, and the value [200 (109) vs.128 (53)] was added to the sample size calculation formula (*n* = 2*[(*α* + *β*) *σ*/*δ*]^2). The sample size will be estimated by considering a sample loss rate of 10%. Then, the sample size was obtained.

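### The primary endpoint bundles tussis with nausea/vomiting and body movement without a combining rule, while the trial's question is tussis and its sample-size figures are for propofol demand

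*Protocol article*

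**What the plan says.** The primary endpoint appears three times in the protocol article. Endpoints has it in the plural: "The primary endpoints include the frequency of tussis, nausea and vomiting, and/or body movements observed at the insertion of the endoscope", extended to 5 minutes after insertion. The Method part of the Abstract also uses the plural. Intervention uses the singular: "The primary outcome was the frequency of tussis, nausea and vomiting, and/or body movements observed at the insertion of the endoscope". None of the three says how the parts are combined.

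The trial's question is stated more narrowly. The title names tussis. The Introduction expects that the combinations, "especially the combination of propofol and esketamine, might reduce tussis incidence". The Discussion describes the aim as reducing the cough reflex. Under Statistical methodology, the multivariate regression is there "to explore the effects of different analgesic drugs combined with propofol on tussis during upper GI endoscopy". That section also lists rank-sum, chi-square and Fisher tests for count data, sets two-sided p < 0.05, and does not say which test belongs to the primary endpoint.

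The Sample size calculation section begins with tussis: esketamine plus propofol "could exhibit significant effect against tussis reduction incidence by a minimum of 15% during upper GI endoscopy". It then changes variable: "based on the 80% power difference of 15% difference in propofol demand". The only values put into its formula are 200 (109) versus 128 (53). Perioperative propofol dose is secondary endpoint (3).

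**The concern.** The wording supports at least three primary analyses: the proportion of patients with any of the listed events, separate tests of each event type, or a comparison of event counts. They answer different questions and can give different conclusions from the same data.

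A composite does not test the tussis hypothesis. Components that the drug leaves alone can hide a real tussis effect, and a fall in body movement or vomiting can produce a positive primary result with no effect on cough. Separate primaries at 0.05 each inflate the type I error. The sample-size section does not settle which reading was meant, because its numbers belong to a different variable.

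**Working it through.** **1. The plan's own sample size.** The section prints no result; 100 per group (400 in total) appears under Intervention and elsewhere. Inputs from Sample size calculation and Statistical methodology: means 200 and 128, so δ = 72; bracketed values 109 and 53 read as SDs; two-sided α = 0.05; power raised to 90%; 10% loss. That these are propofol amounts is inferred from the sentence, which gives no unit or label. The formula is n = 2[(z_α + z_β)σ/δ]², reading its α and β as normal quantiles (1.960 and 1.282).

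| σ used | n per group | after n/(1 − 0.1) |
|---|---|---|
| √[(109² + 53²)/2] = 85.7 | 30 | 34 |
| 109 | 49 | 55 |
| 53 | 12 | 14 |

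Taking δ as 15% of 200 = 30 instead gives 172, 278 and 66 for the same three SDs (192, 309 and 74 after loss). None of these gives 100.

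**2. What 100 per group gives for tussis.** The control rate is not stated, nor whether 15% is absolute or relative. Assume a 15-point absolute fall. Power = Φ[(d − 1.96·s₀)/s₁], where d = p₁ − p₂, p̄ = (p₁ + p₂)/2, s₀ = √[2p̄(1 − p̄)/n] and s₁ = √{[p₁(1 − p₁) + p₂(1 − p₂)]/n}.

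For 30% to 15%: p̄ = 0.225, s₀ = 0.0591, s₁ = 0.0581, and (0.15 − 0.1157)/0.0581 = 0.59, so power is 0.72. In the same way, 20% to 5% gives 0.90, 25% to 10% gives 0.80, 40% to 25% gives 0.62 and 50% to 35% gives 0.57.

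**3. Composite, other events unaffected.** Assume tussis falls from 30% to 15% and other events occur independently in a proportion q of both groups. The composite rate is 1 − (1 − p)(1 − q).

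| q | Composite rates | Difference (points) | Power, n = 100 |
|---|---|---|---|
| 0 | 30.0% vs 15.0% | 15.0 | 0.72 |
| 10% | 37.0% vs 23.5% | 13.5 | 0.55 |
| 30% | 51.0% vs 40.5% | 10.5 | 0.32 |
| 50% | 65.0% vs 57.5% | 7.5 | 0.19 |

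**4. Composite, tussis unaffected.** Assume other events fall from 30% to 15% and tussis stays at 10%, 20% or 30%. The composites are 37.0% vs 23.5%, 44.0% vs 32.0% and 51.0% vs 40.5%. The probability of a significant result is 0.55, 0.42 and 0.32.

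**5. Composite, everything reduced.** Assume tussis falls from 30% to 15% and q also halves. For q = 10%, 30% and 50% the composites are 37.0% vs 19.25%, 51.0% vs 27.75% and 65.0% vs 36.25%. Power at 100 per group is 0.80, 0.93 and 0.99, above the 0.72 for tussis alone.

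**6. Three separate primaries.** For one pairwise contrast with success on any one of the three, the family-wise error is 1 − 0.95³ = 0.143 under independence, and at most 3 × 0.05 = 0.15 under any dependence.

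**The case against.** The strongest reply is that a composite of reflex responses to the endoscope is a sensible endpoint, and the singular wording under Intervention favours it. The Abstract and Introduction say that tussis raises the incidence of nausea and vomiting, and the Introduction credits a propofol-opioid combination with inhibiting throat reflexes. The components may therefore move together, and step 5 shows that the composite can then be the more powerful choice. This stands: dilution is one scenario, not a general result. It does not supply a combining rule or reconcile the endpoint with a hypothesis about tussis.

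This is also a condensed article, and a full protocol or analysis plan may hold a combining or multiplicity rule. A reader might infer that the sponsor is free to choose the reading after seeing the data; the article alone does not establish that. What it does show is a primary endpoint stated in forms that do not agree.

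A reader might also infer that one component cannot be measured, since nausea is a sensation and Intervention says: "The endoscope will be inserted when the eyelash reflex disappeared (sedation depth grade: deep sedation". But nausea and vomiting are listed as one observed item, which can mean visible retching or vomiting, and sedation may vary over the 5 minutes. The wording is loose; the item is not shown to be unmeasurable.

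**Conclusion.** The concern holds. The primary endpoint is an uncombined bundle, while the title, hypothesis and regression concern tussis. As written, the primary test can miss a real tussis effect or be positive without one.

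A reader might take the opening of Sample size calculation to mean that the trial is sized on tussis. It is not: tussis is only the first premise, and the values used belong to what appears to be propofol demand, a secondary endpoint. The planned 100 per group is therefore justified for neither tussis nor the bundle.

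At 100 per group, power falls from 0.72 to between 0.55 and 0.19 when the other events do not respond. A composite driven only by the other events is significant with probability 0.55 to 0.32. These figures rest on assumed event rates and independent components, and the direction reverses if the drug also reduces the other events. The family-wise figure of about 14% is the independence value, not a maximum; the bound is 15%. The ambiguity itself depends on none of these assumptions.

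**What to change.** Name one primary endpoint: any tussis (yes/no) from insertion of the endoscope into the pharyngeal cavity until 5 minutes after insertion. Word it identically in the Abstract, Intervention and Endpoints. Make visible retching or vomiting, body movement, the any-of-three composite and the number of coughs separate secondary endpoints.

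Rewrite Sample size calculation on the tussis endpoint. State the assumed control rate, say whether 15% is absolute or relative, and give the power that 100 per group provides.

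A clearly defined composite would also remove the ambiguity, but the hypothesis, regression and sample size would then have to be rewritten to match it. Tussis is preferred because it is the question the trial already asks.

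The cost is that the other components lose primary status, and that a formal amendment with ethics approval is needed under Ethical considerations, amendments and dissemination. Data collection is unchanged. The amendment should be dated before the database is locked and the statistician is unblinded.

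### Secondary endpoint (2) has two stop events and endpoint (1) carries an unexplained second interval; time to first added propofol also has no value in patients who need no top-up

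*Protocol article*

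**What the plan says.** Endpoints, secondary endpoint (1), is labelled as the time to addition of the first drug and runs "from the end of induction to the addition of the first drug (from the injection of the study medication to the disappearance of eyelash reflex". Endpoint (2), time of recovery from anaesthesia, runs "from the end of the operation till the patient left the recovery room (the end of operation to consciousness return".

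The Intervention section places these events in sequence. Scope insertion waits for the eyelash reflex: "The endoscope will be inserted when the eyelash reflex disappeared (sedation depth grade: deep sedation". Extra dosing is conditional: "Multiple-dose administration is acceptable according to the state of the patient", and during the procedure "2–4 mL of propofol should be added under the conditions of extended operation time, accelerated breathing, and elevated blood pressure and heart rate". In the recovery room, vital signs are recorded "until the patients met the standard of leaving the hospital (Steward score ≥ 4) before discharge".

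Statistical methodology bases efficacy on all randomised patients. It summarises measurement data by mean and standard deviation or by quartiles, and compares them by repeated analysis of variance and the Tukey test. It also says that missing data are not imputed.

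Endpoint (6) covers "MMSE scores, MET scores, and sleep condition after 0.5 h, 2 h, 4 h, 1 day, 2 days, 3 days" and later times. In Assessments, adverse events "will be followed up through phone calls after 0.5 h, 2 h, 1 day, 2 days, 3 days" and later, with no 4 h contact.

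**The concern.** An endpoint needs one start and one stop event. Endpoint (2) has one start and two stops, so two analysts could report different quantities under the same name, or the choice could be made after the data are seen. Endpoint (1) leaves the same doubt unless its bracket is read as a definition of induction.

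A separate difficulty arises if endpoint (1) means time to the first added drug (propofol is the only drug that the Intervention section provides for adding). Top-ups are conditional, so some patients may have none and therefore no recorded time. Comparing only the recorded times would select patients on an event after randomisation that treatment is expected to affect. The Introduction says that propofol alone calls for extra doses and that esketamine lowers propofol doses. Such a comparison would also sit badly with an efficacy population of all randomised patients.

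**Working it through.** **Definitions side by side**

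| Endpoint | Reading | Start | Stop |
|---|---|---|---|
| (1) | main clause | end of induction | first added drug |
| (1) | bracket | study-drug injection | loss of eyelash reflex |
| (2) | main clause | end of operation | leaving the recovery room |
| (2) | bracket | end of operation | return of consciousness |

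*Endpoint (2).* The two stops are different events. Assessments has the MMSE repeated before the patient leaves the recovery room, and a patient who completes an MMSE is already conscious. Return of consciousness therefore comes before exit.

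*Endpoint (1).* The two intervals share neither start nor stop. If induction ends at loss of the eyelash reflex, as the insertion rule suggests, the bracketed interval finishes where the main one begins. The bracket could then be a definition of induction. However, it follows the stop event rather than the word induction, and the parallel bracket in (2) restates the whole interval. The text does not decide between these readings.

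**Illustration of comparing topped-up patients only**

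The article gives no top-up rate and no procedure length for this endpoint, so there is no stated figure to reproduce. Every input below is an assumption: constant hazard λ of a first top-up in the control arm of 0.1, 0.2 or 0.3 per min; hazard ratio 0.5; observation window D of 5, 10 or 15 min from the end of induction.

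- Share with a top-up: 1 − exp(−λD)
- Mean time among topped-up patients: 1/λ − D·exp(−λD)/(1 − exp(−λD))
- Restricted mean over all patients: (1 − exp(−λD))/λ

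Worked case, D = 10, λ = 0.1 (control) and 0.05 (treated):

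- Shares: 1 − 0.368 = 63% and 1 − 0.607 = 39%.
- Topped-up-only means: 10 − 10 × 0.3679/0.6321 = 4.18 min and 20 − 10 × 0.6065/0.3935 = 4.59 min; difference 0.40 min before rounding of the means.
- Restricted means: 0.6321/0.1 = 6.32 min and 0.3935/0.05 = 7.87 min; difference 1.55 min.
- Ratio: 0.40/1.55 = 26%.

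| D (min) | λ control | Topped up, control / treated | Difference, topped-up only (min) | Difference, restricted mean (min) | Ratio |
|---|---|---|---|---|---|
| 5 | 0.1 | 39% / 22% | 0.10 | 0.49 | 21% |
| 5 | 0.2 | 63% / 39% | 0.20 | 0.77 | 26% |
| 5 | 0.3 | 78% / 53% | 0.29 | 0.93 | 32% |
| 10 | 0.1 | 63% / 39% | 0.40 | 1.55 | 26% |
| 10 | 0.2 | 86% / 63% | 0.75 | 2.00 | 37% |
| 10 | 0.3 | 95% / 78% | 0.99 | 2.01 | 49% |
| 15 | 0.1 | 78% / 53% | 0.88 | 2.78 | 32% |
| 15 | 0.2 | 95% / 78% | 1.48 | 3.02 | 49% |
| 15 | 0.3 | 99% / 89% | 1.73 | 2.67 | 65% |

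Ratios are taken before rounding. The topped-up-only comparison gives the smaller difference in every scenario, and most of the difference is lost where top-ups are least common.

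**The 4 h time.** Endpoint (6) has it and the call schedule in Assessments does not. That schedule is worded for adverse events. The next sentence, on sleep, MET, MMSE and HADS, gives no times of its own.

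**The case against.** The strongest reply concerns endpoint (1). Its bracket may simply define induction in the wrong place, leaving one interval that agrees with the label. This stands as a possible reading. A reader might infer that the protocol fixes two incompatible definitions of (1) that point in opposite directions; the text supports only that the definition is unsettled.

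Second, censoring rules are commonly left to an analysis plan, which is not shown, and the article nowhere says that the comparison is limited to topped-up patients or that a patient without a top-up counts as missing. This also stands: the absence of a survival method is not in itself an error. What remains is that the stated summaries, tests and no-imputation rule give such a patient no value. An analysis plan could supply one, but it would first have to choose the interval.

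Third, a reader might infer that the trial would lose sight of propofol sparing. It would not: endpoint (3), perioperative propofol dose, is defined for every patient, with or without a top-up.

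Fourth, one might conclude that the 4 h scores are not collected. Assessments does not establish that, because the schedule without a 4 h contact is the one for adverse events.

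**Conclusion.** The point holds as a defect in stated secondary endpoint definitions. It is firm for endpoint (2), where one label has two stop events. For endpoint (1) it is an ambiguity that needs correcting on either reading.

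The no-value problem applies only to time to first added propofol. Loss of the eyelash reflex should be observed in essentially every patient, because insertion waits for it. The size, 21% to 65% of the restricted-mean difference, rests wholly on assumed constant hazards, a hazard ratio of 0.5 and windows of 5 to 15 min. It shows the direction and plausible scale of the attenuation and does not predict this trial's result.

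The primary endpoint and the sample size are untouched. The 4 h mismatch is a minor matter of aligning two lists. The correction is worth making because it is cheap and removes a choice that could otherwise be made after seeing the data.

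**What to change.** 1. State one start and one stop event for each of endpoints (1) and (2). Either choose one interval for each, or name up to four separately: induction time (study-drug injection to loss of eyelash reflex), time to first added propofol (from end of induction), time to consciousness and time to recovery-room exit (both from end of operation). Define the end of induction explicitly. Choosing one interval is enough to cure the defect; naming all four adds secondary comparisons at the stated p < 0.05.
2. If time to first added propofol is kept, analyse it in all randomised patients, censoring those without a top-up at the end of endoscopy, by Kaplan-Meier with a log-rank test or by Cox regression. This replaces means or quartiles among topped-up patients.
3. Confirm that the times of eyelash-reflex loss, first top-up and return of consciousness are recorded. Assessments lists drug doses, anaesthesia time and operation time, but not expressly these three.
4. Align the 4 h time in endpoint (6) with the follow-up schedule in Assessments, by removing it or by scheduling it.

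The cost is a wording change and a short analysis rule, plus time stamps if they are not already captured, and a 4 h contact only if that time is kept and not already arranged.
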